#### 9.5. Exploratory Objective Analyses

Not applicable.

#### 9.6. Safety Analyses

For the following items, the number of subjects evaluated, the number of events, and the incidence proportion will be calculated.

- Adverse events, adverse drug reactions
- Serious adverse events, serious adverse drug reactions
- Adverse events resulting in death, adverse drug reactions resulting in death
- Adverse events leading to discontinuation of the trial, adverse drug reactions leading to discontinuation of the trial

#### 9.7. Other Analyses

##### 9.7.1. Other Variables and/or Parameters

Not applicable.

##### 9.7.2. Subgroup Analysis

Subgroup analyses will be performed for the following factors and categories. In the subgroup analyses, the same analyses as the primary analysis will be conducted.

| Factor Name                     | Category               |
|---------------------------------|------------------------|
| Cause of sub-macular hemorrhage | AMD, RAM               |
| Dose of tPA formulation         | ≤ 8,000 IU, > 8,000 IU |

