| Physical Characteristics  | clear, colorless liquid                                                                                                                                                                                                                                                                                             |                    | colorless and odorless gases | liquid                      |
| Specification             | One vial (5 mL) containing 400,000 International Units (IU)                                                                                                                                                                                                                                                         | —                  | —                            | —                           |
| Dosage and Administration | Add 5 mL of physiological saline to one vial of monteplase (recombinant), dissolve completely without foaming to obtain a solution of 80,000 IU/mL; administer 0.1 mL (8,000 IU) sub-retinally after vitrectomy. If injection is difficult, the surgeon may, at his/her discretion, reduce the dose as appropriate. | —                  | Intra-ocular injection       | Intra-ocular injection      |
| Administration Frequency  | Once                                                                                                                                                                                                                                                                                                                | Once               | Once                         | Once                        |
| Route of Administration   | Sub-retinal administration                                                                                                                                                                                                                                                                                          | —                  | Intravitreal administration  | Intravitreal administration |

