#### 6.5. Compliance with Trial Intervention

Under medical management, the subject shall receive the trial intervention from the principal investigator, sub-investigator, or a pre-designated responsible individual. The date of intervention, the eye receiving montepase (recombinant), the administered dose, the injection site, the details of positional restriction, and, if the dose is reduced or increased from the stipulated amount (0.1 mL), the reason shall be recorded; for gas tamponade or silicone oil exchange, the material used shall be recorded.

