#### 6.6. Dose Adjustment of Trial Intervention

If, based on the extent of hemorrhage or retinal condition, sub-retinal administration of 0.1 mL is judged to be difficult (e.g., investigational product spreading beyond the retinal vascular arcade) by the principal investigator or sub-investigator, the dose may be reduced as appropriate. Furthermore, after Visit 1, no additional sub-retinal administrations shall be performed except in cases of re-bleeding.

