#### 9.2. Analysis Populations

For the purpose of analysis, the following analysis populations are defined.

| Analysis Population                     | Definition                                                                                                                                                                                           |
|-----------------------------------------|------------------------------------------------------------------------------------------------------------------------------------------------------------------------------------------------------|
| Informed Consent Population             | All subjects who provided informed consent.                                                                                                                                                          |
| Enrolled Population                     | All subjects who were formally enrolled.                                                                                                                                                             |
| Intervention Population                 | Subjects among the enrolled cohort who received the investigational drug. This group constitutes the primary safety analysis set.                                                                    |
| Intervention Discontinuation Population | Subjects among the enrolled cohort whose investigational drug administration was discontinued.                                                                                                       |
| Completion Population                   | Subjects from the trial-intervention population who completed the treatment period and observation period and attended a visit at week 12 (week 12 $\pm$ 7 days).                                    |
| Discontinuation Population              | Subjects from the trial-intervention population whose follow-up during the treatment period or observation period was discontinued and who did not attend a visit at week 12 (week 12 $\pm$ 7 days). |
| FAS (Full Analysis Set)                 | From the Intervention Cases, subjects meeting any of the following criteria are excluded. 
 
● No efficacy data exists after investigational drug
 
     |

|  |                                             |
|--|---------------------------------------------|
|  | administration.
● Serious GCP violation. |

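### The dose subgroup in 9.7.2 is cut at the highest permitted single dose, so it separates overdoses from everyone else and pools reduced with full doses

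*Protocol*

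**What the plan says.** Section 9.7.2 names two subgroup factors. The second is "Dose of tPA formulation", with categories "≤ 8,000 IU, > 8,000 IU". On method it states: "In the subgroup analyses, the same analyses as the primary analysis will be conducted". Under section 9.3.2 that means a 95% CI for the mean change in CFT at Week 1 and a t-test.

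The dosing rules are elsewhere:

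- **Planned dose.** Table 6-1 (section 6.1) has the surgeon "administer 0.1 mL (8,000 IU) sub-retinally after vitrectomy", with a frequency of once.
- **Adjustment.** Table 6-1 allows change in one direction: "If injection is difficult, the surgeon may, at his/her discretion, reduce the dose as appropriate". Section 6.6 gives the ground for it: "If, based on the extent of hemorrhage or retinal condition, sub-retinal administration of 0.1 mL is judged to be difficult", for example because the product spreads too far.
- **Excess.** Section 6.8 classes a dose above 8,000 IU as an overdose.
- **Recording.** Section 6.5 requires that "if the dose is reduced or increased from the stipulated amount (0.1 mL), the reason shall be recorded".
- **Repeat dosing.** Section 6.6 permits further sub-retinal administration only for re-bleeding. Table 3-1 and its footnote treat vitreous re-operation for re-bleeding, with or without sub-retinal tPA, under the composite strategy, and section 9.3.2 then sets the change to 0.
- **Analysis set.** For the FAS, section 9.2 says: "From the Intervention Cases, subjects meeting any of the following criteria are excluded". The two criteria are a lack of post-dose efficacy data and a serious GCP violation. Overdose is not one of them.

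Section 9.7.2 does not say whether dose means the Visit 1 dose or a sum.

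**The concern.** A dose subgroup is useful if it divides subjects along a variation that the protocol expects. Here the cut sits at the ceiling of permitted dosing. A subject treated according to the protocol at Visit 1 can only fall in the lower category, whether the dose was full or reduced.

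This is the only pre-specified look at dose on the primary endpoint. As written, it will either reproduce the primary result or report a handful of deviations or re-treated subjects under the label of a dose effect. The question a reader would want addressed is whether eyes given less than 0.1 mL behaved differently, and this split cannot address it.

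**Working it through.** **Inputs.** Target N = 20, planning mean change -120 µm and SD 170 µm (section 9.9); dose concentration 80,000 IU/mL (Table 6-1); change of 0 for composite events (section 9.3.2). The protocol gives no rate for overdose, re-bleeding, re-dosing or prior tPA, so group sizes below are assumptions shown over a range. All 20 subjects are taken to be in the FAS with a Week 1 value.

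**The plan's own figure.** A one-sample t-test with effect size 0.70, two-sided 5% and 80% power needs n = 19 (noncentral t, power 82.3%). Allowing 5% dropout, 19/0.95 = 20. The stated sample size reproduces.

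**Reading 1: dose at Visit 1.** The planned dose is 0.1 mL × 80,000 IU/mL = 8,000 IU, which falls in the lower category, as does any reduction. If the protocol is followed, the groups are 20 and 0.

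The 95% CI half-width is t(0.975, n-1) × 170/√n:

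| Overdoses | Upper group | Lower group |
|---|---|---|
| 0 | empty | n = 20: 2.093 × 170/√20 = 79.6 µm (same as the primary analysis) |
| 1 | n = 1: no CI | n = 19: 2.101 × 170/√19 = 81.9 µm |
| 2 | n = 2: 12.706 × 170/√2 = 1,527 µm | n = 18: 2.110 × 170/√18 = 84.5 µm |

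If each subject has probability p of exceeding 8,000 IU, the upper group is empty with probability (1-p)^20. It reaches the two subjects needed for a t-test with probability 1 - (1-p)^20 - 20p(1-p)^19:

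| Assumed p | Expected n | P(n = 0) | P(n ≥ 2) |
|---|---|---|---|
| 1% | 0.2 | 82% | 2% |
| 5% | 1 | 36% | 26% |
| 10% | 2 | 12% | 61% |
| 20% | 4 | 1% | 93% |

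At the planning mean and SD, power is 7% with n = 2 and 17% with n = 4.

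**Reading 2: doses summed.** Two full sub-retinal doses total 16,000 IU, above the cut. Two half doses (0.05 + 0.05 mL) total 8,000 IU and stay below it. The upper group could then hold several kinds of subject:

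- *Re-operated with sub-retinal tPA for re-bleeding before Week 1:* change set to 0. If the whole group is of this kind, the SD is 0 and the t statistic is 0/0, undefined.
- *Re-dosed after Week 1:* the Week 1 value is as observed, but the subject is classified by a dose given after the endpoint was measured.
- *Prior intravitreal tPA for this hemorrhage* (recorded under section 6.9.1, and no exclusion criterion names it), *or tPA for another disease* (treatment policy in Table 3-1): observed values are kept.

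If k subjects are set to 0 and m have observed values averaging the planned -120 µm, the expected group mean is -120 × m/(k+m). For a group of four:

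- k = 1, m = 3: -90 µm
- k = 2, m = 2: -60 µm
- k = 3, m = 1: -30 µm

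These differences from -120 µm come from the imputation rule alone. With no imputed values the mean is not distorted, but the half-width is still 1,527 µm at n = 2, 422 µm at n = 3 (4.303 × 170/√3) and 271 µm at n = 4 (3.182 × 170/√4).

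**The case against.** The strongest counter-argument is that the factor is the dose of tPA formulation, not the Visit 1 monteplase dose. An analysis plan could define it as total tPA for the hemorrhage. A full trial dose plus any prior intravitreal tPA would then fall in the upper group: a real exposure, fixed before the endpoint, with observed values. This part stands. A reader might infer that no definition of dose could make the row informative, or that a summed upper group would consist mainly of re-bleeders. The protocol supports neither, because it gives no rates. What remains is that such a group mixes routes, indications and timings, and so does not isolate the trial dose.

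Second, the upper row may be a contingency for deviations. Section 6.5 does foresee a recorded increase, and after an overdose the lower group shows the result without the overdosed eyes. That is a fair use, but a listing serves it better than a t-test on one or two subjects.

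Third, small groups are not peculiar to this row. Section 9.9 guarantees only three subjects per cause, so the 422 µm at n = 3 applies there too. This is correct; the defect here is where the cut lies, not imprecision alone.

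Finally, a reader might infer that section 6.8 turns a permitted repeat dose into an overdose. Its natural sense is a single administration, and section 6.6 expressly allows repeats for re-bleeding. The naming of alteplase in section 6.8 recurs in Table 3-1 and section 6.9.2.1. It is a document-wide clerical slip, separate from this point.

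**Conclusion.** The point holds at minor severity. For the Visit 1 dose, the cut in section 9.7.2 coincides with the maximum permitted single dose. The upper group is expected to be empty apart from deviations, the lower group is all or nearly all of the FAS, and full and reduced doses are pooled. This follows from the protocol's own dosing rules and needs no assumed rate.

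For a summed dose the conclusion is weaker. The group would be a mixture whose size and make-up cannot be predicted from the document, and it would not estimate the effect of the trial dose. The figures for that reading are illustrations. They rest on assumed counts, the planning SD of 170 µm, and observed subjects averaging -120 µm.

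An analysis plan may define how dose is counted, but the categories themselves are fixed in the protocol. The primary analysis and N = 20 are not affected.

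**What to change.** In section 9.7.2, replace the dose row with: *Dose of monteplase given at Visit 1: 8,000 IU (full), < 8,000 IU (reduced)*.

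Report it descriptively, without a test. Reduction depends on the extent of hemorrhage or the retinal condition (section 6.6), so the comparison is confounded with severity, and the reduced group may be small. List separately any subject given more than 8,000 IU in one administration or re-dosed for re-bleeding.

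The cost is one table row and a sentence on reporting. No new data are needed: the Visit 1 dose is recorded under section 6.5 and any sub-retinal dose for re-bleeding under section 8.2.7. Deleting the row would also remove the defect, but would leave no planned look at reduced dosing.

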#### 9.8. Interim Analysis

No interim analysis is planned for this clinical trial.

#### 9.9. Determination of Sample Size

- Target number of subjects: 20 (however, a minimum of three subjects must be enrolled for each disease, AMD and RAM)

Rationale for the target: In a retrospective review of our institution over the past approximately two years, eight patients (11 eyes) who received sub-retinal tPA for SMH with a pre-treatment CFT  $\geq 300$   $\mu\text{m}$  were identified. The change in CFT at one week post-procedure had a mean of  $-109.36$   $\mu\text{m}$  and a standard deviation of  $176.98$   $\mu\text{m}$  (unpublished data). The corresponding

effect size  $d$  was 0.62 (effect size  $d = \text{mean difference} / \text{SD}$ ). Because SMH patients meet the criteria for a rare disease and because this trial will enroll patients with at least a moderate amount of hemorrhage and at least a moderate visual-acuity loss, a modest clinical improvement is anticipated. Assuming an effect size of 0.7 (mean change  $-120 \mu\text{m}$ , SD  $170 \mu\text{m}$ ), a two-sided  $\alpha$  of 5 % and 80 % power, the required sample size was calculated to be 19 subjects. Allowing for a 5 % dropout rate, the total target sample size was set at 20 subjects.

## 10. Appendix

### Appendix 1:

#### 10.1. General Considerations Regarding Regulation, Ethics, and Trial Management

##### 10.1.1. Regulatory and Ethical Considerations

This clinical trial will be conducted in compliance with the following laws, regulations, and standards:

- ✓ The ethical principles of the Declaration of Helsinki (1964) and its revisions
- ✓ The standards stipulated in Article 14, Paragraph 3 and Article 80-2 of the Pharmaceuticals and Medical Devices Act
- ✓ The “Ordinance on Standards for Conducting Clinical Trials of Pharmaceuticals (Good Clinical Practice, GCP)” (Ministry of Health, Labour and Welfare Ordinance No. 28 of 27 March 1997) and its amended ordinances and related guidance
- ✓ Standard Operating Procedures
- ✓ This clinical trial protocol

##### 10.1.2. Compliance with the Trial Protocol, Deviations, and Amendments

###### 10.1.2.1. Compliance with the Clinical Trial Protocol

The principal investigator shall submit the clinical trial protocol and GCP-required documents such as the explanatory material and informed-consent form to the head of the trial site and obtain written approval for conducting the trial. The principal investigator, sub-investigators, and trial collaborators shall conduct the trial in accordance with the clinical trial protocol.

###### 10.1.2.2. Deviations from the Clinical Trial Protocol

Except in the following cases, the principal investigator or sub-investigator shall not deviate from or amend the clinical trial protocol without obtaining prior written approval based on review by the Institutional Review Board (IRB):

- 1) When it is medically unavoidable, such as to avoid an imminent danger to a subject;
- 2) When the change concerns only administrative matters of the trial.

In case of 1), the principal investigator shall, as soon as possible, submit to the head of the trial site and the IRB the details and reasons for the deviation or amendment, and, if appropriate, a draft of the revised protocol, and obtain approval.

The principal investigator shall document and retain in writing all actions that deviate from the

clinical trial protocol.

#### 10.1.3. Amendments to the Clinical Trial Protocol

If the principal investigator determines that amendment of the clinical trial protocol is necessary, or if the IRB directs an amendment, the trial coordinating physician shall amend the protocol. The principal investigator shall report the amendment content and its rationale to the head of the trial site and obtain IRB approval.

The amendment procedure shall follow the “Procedures for Preparation of the Clinical Trial Protocol.”

#### 10.1.4. Institutional Review Board

##### 10.1.4.1. Review of Clinical Trial Conduct

The appropriateness of conducting this trial shall be reviewed by the Institutional Review Board from ethical, scientific, and medical/pharmacological perspectives. The trial will be conducted only after obtaining IRB approval. If the IRB directs any modifications to the informed-consent document or other materials, the principal investigator at the respective medical institution shall address them.

##### 10.1.4.2. Continuing Review

The principal investigator shall submit, in writing to the head of the trial site, a summary of the current status of the trial at least annually, or more frequently as requested by the IRB, in order to undergo the IRB’s continuing review. The head of the trial site shall obtain the IRB’s opinion regarding the appropriateness of continuing the trial at that site.

#### 10.1.5. Procedures for Explanation and Obtaining Informed Consent

##### 10.1.5.1. Preparation of the Explanation Document and Informed Consent Form

The principal investigator shall prepare the explanation document and the informed consent form and obtain prior approval from the IRB. The items to be included in the explanation document shall be prepared in accordance with Article 51 of the Ordinance on Standards for Conducting Clinical Trials of Pharmaceuticals and its accompanying guidance.

##### 10.1.5.2. Obtaining Consent

The principal investigator or sub-investigator shall, prior to a patient’s participation in the trial, provide a thorough explanation using the explanation document, confirm that the patient has

fully understood the content, and obtain the patient's voluntary written consent to participate. The patient who has received the explanation shall, after fully understanding the content of the explanation document, sign or affix a seal to the informed consent form indicating agreement to participate in the trial and date it. The principal investigator or sub-investigator who provided the explanation shall, after confirming the patient's comprehension of the explanation document, also sign or affix a seal to the same informed consent form and date it. If a trial collaborator provides supplemental explanation, that collaborator shall likewise sign or affix a seal and date the form.

The principal investigator or sub-investigator shall deliver the signed informed consent form and the explanation document to the subject and shall retain the original informed consent form in the medical institution's records.

#### 10.1.5.3. Notification to Other Institutions at the Time of Consent

The principal investigator or sub-investigator shall ascertain whether the subject is receiving care at another hospital or department; if so, after obtaining the subject's consent, the investigator shall notify the subject's attending physician of the subject's participation in this trial.

#### 10.1.5.4. Points to Consider When Obtaining Consent

When obtaining consent, the following points shall be observed.

- ✓ The principal investigator or sub-investigator shall explain the trial using plain language that enables the patient to understand the study details.
- ✓ The principal investigator or sub-investigator must not coerce the patient to participate in or continue the study, nor exert undue influence on the patient's decision.
- ✓ The principal investigator or sub-investigator shall, after providing the explanation, give the patient an opportunity to ask questions, continue the explanation until the patient is satisfied, and allow sufficient time for the patient to decide on participation.
- ✓ The principal investigator or sub-investigator shall specify the visit date to the patient, explain that investigations/observations will be performed, and obtain the patient's consent.
- ✓ In the explanation, no language should be used that would cause the subject to waive or doubt his/her rights, or that would exempt or cast doubt on the legal responsibility of the principal investigator or the trial site.
- ✓ In this clinical trial, obtaining consent through a proxy is not permitted.
- ✓ If a subject has difficulty reading the informed-consent document because of reduced visual acuity, visual field, or other visual-function impairment, a neutral witness shall be required during the explanation to the subject. A neutral witness must be independent of

- the conduct of this trial and must not be unduly influenced by persons involved in the trial.
- ✓ Subjects undergoing rescreening must sign a new informed-consent document.

#### 10.1.5.5. Revision of the Informed-Consent Document

If new information is obtained that may affect a subject's decision to continue participation in the trial, the principal investigator or sub-investigator shall promptly convey this information to the subject, confirm the subject's intention regarding continued participation, and record it. The principal investigator shall also promptly revise the informed-consent document based on the new information, submit the revised document to the head of the trial site, and obtain approval from the Institutional Review Board. The principal investigator or sub-investigator shall use the revised informed-consent document to provide a thorough explanation to the subject, reconfirm the subject's intention to continue participation, and obtain written consent.

